**Primary Study Aim 1: The effect of male involvement on women’s adherence to condoms, diaphragm and gel.**

The association between the degree of male involvement and adherence will be examined by the development of a categorical scale for *reported* adherence level to each study product (diaphragm, gel, condoms) during sex. Analysis of adherence will be stratified by study arm as this might confound degree of male involvement (i.e. women in condoms arm are more likely to have discussed study products with partner since he is more involved in using them). It is possible that this association may be confounded, i.e. male involvement may be lower in couples with ‘limited’ education and those with ‘limited’ education may have the lowest adherence, resulting in a spurious association between male involvement and adherence. In order to account for this, and other potentially confounding variables, a multivariate analysis will be conducted using a multiple logistic regression model in the SAS statistical package.

Focus groups and in-depth interviews with men and women may give additional insight into the association between male involvement and adherence. As described above, qualitative data will be used to define appropriate measures of “male involvement” that will be used as independent predictors of reported study product adherence. Qualitative data will inform the understanding of the outcome variable of adherence in several ways. Study participants and their partners will be asked and probed on what factors contributed to their use and non-use of each product in an open-ended fashion. Responses will complement the quantitative findings, add new information and possibly clarify discordances in the quantitative data. Qualitative findings may inform the addition of potentially confounding variables in the multivariate model, i.e. if focus group respondents mentioned that being a vegetarian was the most important determinant of diaphragm use, the model would control for dietary preference.

**Power Calculations/ Sample Size considerations for Adherence Analysis**

The MIRA sample size for the Zimbabwe site is 2500. Assuming 10% loss-to-follow-up and accounting for missing data for an additional 13 women who had already completed Month 12 before the initiation of the Male Involvement Study, the expected sample size for analysis of the association between male involvement and adherence is 2237 – 1118 in each arm of the study. The table below lists the power of the study to detect a difference in the high male involvement women vs. low male involvement, considering three ratios of high vs. low male involvement in the study population: 80/20; 60/40 and 50/50. In these calculations, three adherence level scenarios are also considered, where 90%, 70% and 50% of women with high male involvement also have “high adherence”, defined as >80% of sex acts covered by study products.

The table presents the minimum detectable relative percent difference in adherence level that the study will be able to detect with 95% confidence and 90% power between the high male involvement and low male involvement groups. In summary, the sample of 1118 women will have a high degree of power to measure relatively small differences in diaphragm and gel adherence reduction between those with high vs. low male involvement, depending on the scenarios. Condom adherence will be examined in both arms of the study, thereby doubling the available sample size and increasing the power further. In high prevalence settings, a relative “improvement” in adherence of as little as 20% between the high male involvement and low male involvement groups could have substantial public health importance and translate into thousands of infections averted, insofar as increased adherence implies a reduced probability of disease acquisition. Certainly there are other factors to consider, but willingness and ability to use disease prevention methods is a critical first step, and enhanced male involvement is a low-tech and potentially inexpensive intervention approach.

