## 3.4 Preliminary Study

We completed a diaphragm acceptability study among Zimbabwean women who were unsuccessful condom users, which included documentation of problems associated with diaphragm use. Women first enrolled in a 2-month condom intervention phase. Inconsistent condom users were then enrolled into the diaphragm acceptability phase and received a diaphragm educational session, including practice on how to insert the device and use it with KY jelly, which was followed by a booster session 2 months later. Women were followed every 2 months for a total of 6 months. As of March 2003, 840 women were screened and 405 enrolled into phase I over a 12-month period. 189 women enrolled into the diaphragm acceptability phase. 181 women completed the study and the follow up rate was 96%. Diaphragm uptake was almost universal following the intervention and stayed high over time. Consistent use was reported by close to half the sample despite its stated unknown efficacy against HIV/STIs. Both surveys and exit focus group data indicated that the diaphragm was well accepted by both female and male partners and few reported side effects. Problems associated with use—mainly pain or discomfort—decreased over time as women became more familiar with the product and declined from 24% to 5% at the last follow-up visit.

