**Table 2. Power calculations for outcome of effect of male involvement on adherence and acceptability**

| **Minimum absolute percent reduction in women’s diaphragm, gel and condom adherence/ acceptability levels necessary to detect a significant difference resulting from low male involvement with 95% confidence and 90% power under three exposure and outcome scenarios, n = 2237 (1118 per arm)** | | | |
| --- | --- | --- | --- |
| **Amongst those with high male involvement, proportion of women with high adherence**  **(≥ 80% of sex acts covered)or high acceptability** | **Ratio of women with high male involvement: low male involvement** | | |
| **20:80** | **40:60** | **50:50** |
| **90%** | 9% | 7% | 7% |
| **70%** | 12% | 10% | 10% |
| **50%** | 13% | 10% | 10% |

(Computed using Intercooled STATA, 8.2)

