**Primary Study Aim 2: The effect of male involvement on women’s acceptability of condoms, diaphragm and gel**

Acceptability of study products will be measured quantitatively in the MIRA trial by a combination of variables on the interviewer-administered Acceptability Form, the Clinical Follow-Up Form, and the ACASI questionnaires. The relationship between degree of male involvement and study product acceptability and will be studied in the same fashion as the adherence analysis above, and power calculations were computed using the same assumptions in Table 2. For acceptability, it was estimated that among women with high male involvement, 90% will have reported “high acceptability” of the diaphragm and gel. This estimate is based on the results of the Diaphragm Acceptability Study conducted in Zimbabwe prior to the MIRA trial.86 Thus this study will have 95% confidence and 90% power to detect an absolute percent reduction of 7-9% in the group with lower male involvement (see row 1 of Table 2 above). It is anticipated that the difference in diaphragm acceptability will be high regardless of male involvement but that condom and gel acceptability will probably be more affected by male involvement. Looking at the second and third rows in the table, the acceptability of gel and condoms amongst those with high male involvement may be closer to 50% or 70%, thus the study will have 90% power to detect an absolute reduction in acceptability of 10-12%. It is difficult to make a causal connection between an “improvement” in product acceptability and public health outcome – just because an individual reports liking a product does not mean it is used, nor that it is effective. Conversely, an individual might dislike a product (i.e. condoms) but still use them consistently for other reasons, like disease prevention. Nonetheless, acceptability is an important component of use, and it could again be argued that a relatively small improvement in acceptability indicators, such as 20% higher acceptability in the high male involvement group compared to the low male involvement group, could have important public health benefits. Similar to the adherence analysis, qualitative data will inform the examination of the association between male involvement and acceptability of each product. Qualitative data may complement or contradict the quantitative findings, and will add insight into observed relationships.

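### Appendix 16.7: one sentence labels Table 2's detectable differences as relative, but the table and the arithmetic show that they are absolute percentage points

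*Protocol*

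**What the plan says.** Three places in Appendix 16.7 describe the same nine numbers.

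- The adherence power section describes each tabulated value as a "minimum detectable relative percent difference in adherence level that the study will be able to detect with 95% confidence and 90% power". It adds that "the sample of 1118 women will have a high degree of power to measure relatively small differences in diaphragm and gel adherence reduction", depending on the scenario. It then names a relative improvement of 20% between the involvement groups as one that could matter for public health.
- The heading of Table 2 reads "Minimum absolute percent reduction in women’s diaphragm, gel and condom adherence/ acceptability levels necessary to detect a significant difference", and it continues "with 95% confidence and 90% power under three exposure and outcome scenarios, n = 2237 (1118 per arm").
- Primary Study Aim 2 takes the table as absolute twice. For row 1 it cites "95% confidence and 90% power to detect an absolute percent reduction of 7-9% in the group with lower male involvement". For rows 2 and 3 it says that "the study will have 90% power to detect an absolute reduction in acceptability of 10-12" per cent.

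The printed cells, for ratios 20:80, 40:60 and 50:50, are 9/7/7 (90% row), 12/10/10 (70% row) and 13/10/10 (50% row).

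**The concern.** Relative and absolute are different scales for the same cells, and the gap widens as the reference proportion falls. At 90% adherence they nearly coincide. At 50% an absolute difference of 10 points is a 20% relative reduction.

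The paragraph that uses the wrong label also supplies a relative yardstick of 20%. A reader who believes the table is relative sees 10-13% in the 50% row and concludes that a 20% relative effect is well covered in every scenario. It is not, so a null adherence result near 50% use could be given more weight than it deserves.

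The 50% row is one of the protocol's own scenarios. Section 3.4 gives it some relevance: "Consistent use was reported by close to half the sample" in the preliminary study. Section 8.5 also mentions compliance below expectation, without a figure.

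A second slip is that the acceptability text gives 10-12% for rows 2 and 3, although row 3 reaches 13%.

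**Working it through.** **Inputs (Appendix 16.7).** Diaphragm and gel adherence: N = 1,118, one arm. Condom adherence: both arms, N = 2,237 (2,500 × 0.90 − 13). Reference proportion with high adherence, p1 = 0.90, 0.70 or 0.50. Confidence 95%, taken as two-sided because the appendix does not say; power 90%.

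**Formula.** Two independent proportions, normal approximation, groups n1 and n2 set by the ratio, pooled proportion p:

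SE0 = √[p(1−p)(1/n1 + 1/n2)]; SE1 = √[p1(1−p1)/n1 + p2(1−p2)/n2]; power = Φ[(|p1−p2| − 1.96·SE0)/SE1].

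**One cell in full (50% row, 50:50, n1 = n2 = 559, printed 10).**

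- Absolute: 50% against 40%. SE0 = 0.02976, SE1 = 0.02961. (0.10 − 0.05832)/0.02961 = 1.41, so power is 92%.
- Relative: 50% against 45%. SE0 = 0.02987, SE1 = 0.02983. (0.05 − 0.05855)/0.02983 = −0.29, so power is 39%.

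**All cells, in the order 20:80 / 40:60 / 50:50.**

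| Row | Printed | Absolute points for 90% power, N = 1,118 | Power %, printed value as absolute, N = 1,118 | Power %, printed value as relative, N = 1,118 | Power %, printed value as relative, N = 2,237 |
|---|---|---|---|---|---|
| 90% | 9/7/7 | 8.6/6.8/6.6 | 92.6/91.8/93.0 | 86.8/86.0/87.7 | 99.4/99.1/99.3 |
| 70% | 12/10/10 | 11.6/9.4/9.2 | 91.8/93.1/94.0 | 65.0/67.8/69.9 | 91.8/93.0/94.0 |
| 50% | 13/10/10 | 12.0/9.8/9.6 | 94.2/91.0/92.0 | 41.6/37.5/38.7 | 69.5/64.1/65.8 |

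The absolute reading with 1,118 women reproduces the table to within about one point, with power of at least 90% in every cell. A continuity correction adds about 0.2-0.3 points. The relative reading fits no single sample size: with 2,237 women it happens to match the 70% row but gives 99% in the 90% row and 64-70% in the 50% row. The text states the ratios as 80/20 and 60/40, the table as 20:80 and 40:60; reversing them changes little (the 90% row at 20:80 read as relative becomes 89.1%).

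**Relative equivalents of the printed cells.** 90% row: 7/90 to 9/90 = 8-10%. 70% row: 10/70 to 12/70 = 14-17%. 50% row: 10/50 to 13/50 = 20-26%.

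**Power for a 20% relative difference, N = 1,118.** The 20% can be an improvement over the low-involvement group (p2 = p1/1.2) or a reduction from the high-involvement group (p2 = 0.8·p1).

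| Row | Improvement, 20:80/40:60/50:50 | Reduction, 20:80/40:60/50:50 |
|---|---|---|
| 50% (41.7% or 40% against 50%) | 61/78/80% | 77/91/92% |
| 70% | 90/98/98% | 97/99.8/99.8% |
| 90% | about 100% | about 100% |

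**The case against.** The best defence is that this is one wrong word. The table heading directly below it and the acceptability text both say absolute, the calculation is right, and a careful reader would resolve the conflict correctly. That stands.

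Two stronger readings are tempting, and the documents support neither.

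- A reader might infer that the sub-study's power really is 37-42%. It is not. That figure describes only the mislabelled sentence taken literally, in the lowest row and in one arm. For condoms in both arms the same misreading gives 64-70%.
- A reader might infer that the protocol promises 90% power for the 20% improvement. It does not. The 20% is a remark on public health relevance, and the power claim is qualified by scenario. Nor does the appendix set a rule for interpreting a null result.

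It is also fair to say that the shortfall against 20% is confined to the 50% row. The support for that row is indirect: the preliminary study enrolled inconsistent condom users, and consistent use is not the same measure as 80% of acts covered among women with involved partners. The 26% upper end of the relative equivalents also reflects whole-number printing, since the unrounded value is about 24%.

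What remains is that the stated scale is wrong in the power statement for a primary aim of the sub-study, beside a yardstick on that same scale.

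**Conclusion.** The point holds as a labelling error with a limited consequence. Table 2 is correct as absolute points for 1,118 women. Taken as the adherence text states, power for diaphragm and gel would be 86-89%, 65-70% and 37-42% in the three rows, not 90%.

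The practical effect is in the 50% row. There a 20% relative difference does not have 90% power in every ratio scenario: at 20:80 it falls short in either direction, and at 40:60 and 50:50 it falls short when read as an improvement over the low-involvement group. In the 70% and 90% rows power for 20% is at least 90%.

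This rests on a two-sided 5% test of two proportions without continuity correction. It concerns an ancillary study and does not touch the HIV endpoint.

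**What to change.** In the adherence power section, change relative to absolute. Add the relative equivalents of the table values (reductions of about 8-10%, 14-17% and 20-26% in the 90%, 70% and 50% rows). Note that at 50% diaphragm or gel adherence a 20% relative difference does not have 90% power in every ratio scenario, and say in which direction the 20% is measured. In Primary Study Aim 2, change 10-12% to 10-13%. While editing, give the involvement ratios in the same order in text and table.

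The cost is a few words in Appendix 16.7. No sample size, analysis or trial procedure changes; the stated sensitivity at 50% adherence simply reads less favourably.

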**Table 2. Power calculations for outcome of effect of male involvement on adherence and acceptability**

| **Minimum absolute percent reduction in women’s diaphragm, gel and condom adherence/ acceptability levels necessary to detect a significant difference resulting from low male involvement with 95% confidence and 90% power under three exposure and outcome scenarios, n = 2237 (1118 per arm)** | | | |
| --- | --- | --- | --- |
| **Amongst those with high male involvement, proportion of women with high adherence**  **(≥ 80% of sex acts covered)or high acceptability** | **Ratio of women with high male involvement: low male involvement** | | |
| **20:80** | **40:60** | **50:50** |
| **90%** | 9% | 7% | 7% |
| **70%** | 12% | 10% | 10% |
| **50%** | 13% | 10% | 10% |

(Computed using Intercooled STATA, 8.2)

**Primary Study Aim 2: The effect of male involvement on women’s acceptability of condoms, diaphragm and gel**

Acceptability of study products will be measured quantitatively in the MIRA trial by a combination of variables on the interviewer-administered Acceptability Form, the Clinical Follow-Up Form, and the ACASI questionnaires. The relationship between degree of male involvement and study product acceptability and will be studied in the same fashion as the adherence analysis above, and power calculations were computed using the same assumptions in Table 2. For acceptability, it was estimated that among women with high male involvement, 90% will have reported “high acceptability” of the diaphragm and gel. This estimate is based on the results of the Diaphragm Acceptability Study conducted in Zimbabwe prior to the MIRA trial.86 Thus this study will have 95% confidence and 90% power to detect an absolute percent reduction of 7-9% in the group with lower male involvement (see row 1 of Table 2 above). It is anticipated that the difference in diaphragm acceptability will be high regardless of male involvement but that condom and gel acceptability will probably be more affected by male involvement. Looking at the second and third rows in the table, the acceptability of gel and condoms amongst those with high male involvement may be closer to 50% or 70%, thus the study will have 90% power to detect an absolute reduction in acceptability of 10-12%. It is difficult to make a causal connection between an “improvement” in product acceptability and public health outcome – just because an individual reports liking a product does not mean it is used, nor that it is effective. Conversely, an individual might dislike a product (i.e. condoms) but still use them consistently for other reasons, like disease prevention. Nonetheless, acceptability is an important component of use, and it could again be argued that a relatively small improvement in acceptability indicators, such as 20% higher acceptability in the high male involvement group compared to the low male involvement group, could have important public health benefits. Similar to the adherence analysis, qualitative data will inform the examination of the association between male involvement and acceptability of each product. Qualitative data may complement or contradict the quantitative findings, and will add insight into observed relationships.

***Secondary Study Aim 1: Impact of more active male promotion on a) level of male involvement and b) women’s adherence and acceptability of products***

This component of the analysis will evaluate the success of intervention efforts to promote male involvement in the research studies through invitation letters and study ID cards for men. The intervention uptake rate will be tabulated, including a breakdown of whether men came to the clinic, accessed counselling and/or testing for STIs and/or HIV. In the qualitative portion, the study will explore reasons for coming/not coming, and what would have encouraged him, etc. A comparison of characteristics of women whose partners came/did not come will be conducted through bivariate and multivariate analyses. Secondly, this analysis will aim to address whether men coming to the research clinic, as encouraged, had a significant effect on women’s product usage or acceptability, in other words, to evaluate the effect of the intervention.

***Secondary Study Aim 2: Correlates of high vs. low male involvement among women***

In this analysis, a comparison of the characteristics of women who have more involved partners vs. less involved partners will be conducted. A multi-variate logistic regression analysis will examine predictors, such as age, educational status, religion, parity, SES, partner age differential, etc. correlated with degrees of male involvement, controlling got potentially confounding variables. This will help identify the independent characteristics of women who are more “at risk” of non-involved partners.

***Secondary Study Aim 3: Examine an association between male involvement and biological outcomes***

It would be interesting to examine the relationship between male involvement and the incidence of HIV and STIs. However, because these incidence rates are small, there is not enough power in this Male Involvement Study to measure the effect of male involvement on these biological outcomes. However, a composite variable of *any* incident infection (HIV or STI) could be created and correlated with degree of male involvement. It is estimated that HIV incidence in this population will be 4%, and that incidence of chlamydia, gonorrhea and trichomoniasis will be between 2-7% each. Allowing for overlap, whereby someone who has an incident case of gonorrhea may also have Chlamydia and/or seroconvert for HIV, the combined incidence for *any STI* will be 8%, and therefore any STI and HIV = 12%. Assuming this combined level of incidence is observed, this study will have 90% power and 95% confidence to detect a 50% relative reduction from 12% to 6% amongst those with high male involvement compared to low male involvement, under the three ratio scenarios of high vs. low male involvement in the population (80/20; 60/40; 50/50). The study will not have enough power to detect a smaller reduction in biological outcomes between those with high involvement vs. low involvement, unless the ratio of women in the study with high vs. low male involvement is close to 50/50. It is therefore not guaranteed that this study will be able to draw any significant conclusions about this association, but may be able to suggest some relationships that would warrant further investigation.

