## STI and RTI Diagnosis and Treatment

As described in Sections 9.3 and 9.4, we test all women who are eligible for the trial and choose to participate for HIV and other STIs. Women who are laboratory positive for *Chlamydia trachomatis* and/or *Neisseria gonorrhoeae* complete treatment before they are enrolled. Women who have a diagnosed or suspected current STI or reproductive tract infection at enrollment including laboratory diagnosed *Trichomonas vaginalis* and/or *Treponema pallidum* are provided treatment and enrolled. Throughout the study, we collect specimens for STI testing at each follow-up visit. We contact and inform infected women of their results. We provide them with STI treatment in accordance with WHO guidelines free of charge and offer STI testing and treatment for their partners. We pay special attention to possible urinary tract infections (UTIs) because of the association between such infections and diaphragm use.31,32 The study pays for the treatment of incident UTIs diagnosed during the study period.

For other medical conditions identified during study screening and/or follow-up procedures, we refer participants to other sources of care available in their communities. In certain cases of infections or epithelial lesions, the study clinician may decide to interrupt diaphragm and gel use.

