**Secondary aims**

1. To examine whether a small intervention promoting male involvement through invitation letters and male ID cards makes an impact on a) level of male involvement; b) women’s adherence and acceptability.
2. To examine correlates of “high” vs. “low” involvement of male partners, using female and male demographic, behavioural, clinical and attitudinal data.
3. To measure whether there is an association between male involvement and STI/ HIV incidence.
4. To measure whether there is a change in different components of male involvement over time.

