| *Study* | **Data collection time points** | | | |
| --- | --- | --- | --- | --- |
| **Month 3** | **Month 6** | **Month 12** | **Total sample** |
| *MIRA** | 1160 | NA | 2237 | **3397** |
| ***TOTAL SAMPLE*** | ***1160*** | ***116*** | ***2237*** | ***3602*** |

*Form administered after start of MIRA study, therefore approx. half of the participants had already passed the Month 3 visit, and only 15 had completed the Month 12 visits. Form administered at next subsequent visit if scheduled visit missed. Estimates include 10% projected loss-to-follow-up.

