**Frequency and Degree of Male Involvement**

There is no standardized way of measuring male involvement, therefore a necessary first step of the analysis is to further define what male involvement is. This will be explored by tabulating the frequency and degree of male involvement reported by female participants on the Male Partner Involvement Form. These will be descriptive statistics of the proportion of female participants, together with 95% confidence intervals, who report that her partner is supportive, aware of her study participation, like the products, participate in the use of products, etc. Social science data will be coded for descriptions of what male involvement is in women’s own words, including evidence of high vs. low and negative/positive involvement. This should help to expand upon, corroborate and clarify the quantitative data. Service statistics and proxy measures of male involvement (described above) will also be tabulated to contribute to this analysis. These statistics will capture which male partners have come to the clinics, and which services, i.e. counselling, treatment, testing, they have accessed.

Salient features of “male involvement” should emerge from this exercise, such that key variables representing higher vs. lower or positive vs. negative “male involvement” may become evident. Composite variables may be constructed that incorporate more than one binary outcome. These variables will be considered as independent predictors in further analysis of acceptability, adherence and biological outcomes. These measures are not pre-constructed, and have not yet been formally validated. In the analysis process, tests of construct validity will be done, whereby individual questions are correlated with hypothesized outcomes in order to gauge their validity.

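### Male Involvement Study, Aim 3: involvement is correlated with any incident HIV or STI infection without requiring that it be measured first, so an infection can raise measured involvement and bias the association

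*Protocol*

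**What the plan says.** The Male Involvement Study lists as a secondary aim "To measure whether there is an association between male involvement and STI/ HIV incidence". Its analysis section for that aim proposes that a composite of any "incident infection (HIV or STI) could be created and correlated with degree of male involvement". It puts the combined incidence at "therefore any STI and HIV = 12" per cent and states that "this study will have 90% power and 95% confidence to detect a 50% relative reduction from 12% to 6" per cent, under three splits of high to low involvement (80/20, 60/40, 50/50).

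The involvement variables are to be worked out from the Male Partner Involvement Form, service statistics and proxy measures (Frequency and Degree of Male Involvement). Of the service statistics it says: "These statistics will capture which male partners have come to the clinics, and which services, i.e. counselling, treatment, testing, they have accessed". Of the resulting variables: "These variables will be considered as independent predictors in further analysis of acceptability, adherence and biological outcomes". The form is given at Months 3 and 12. The footnote to the appendix's Table 1 notes that "approx. half of the participants had already passed the Month 3 visit" when it was introduced. The table expects 1,160 Month 3 forms and 2,237 Month 12 forms.

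The main protocol ties partner contact to the woman's result. Section 9.3 has partners of women with laboratory-confirmed gonorrhoea, chlamydia or trichomoniasis notified. Section 9.8 says of infected women: "We provide them with STI treatment in accordance with WHO guidelines free of charge and offer STI testing and treatment for their partners". Section 9.10 provides that partner treatment at the study clinic.

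**The concern.** Read together, these sections form a loop. A positive test brings the partner to the clinic or prompts an invitation to him. That contact can count as involvement. Involvement is then used to predict the same positive test. The planned analysis fixes no order in time, and for about half of the women the only form comes a year into follow-up.

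The test then asks whether there is an association in either direction, which is not the question of interest. An association produced by the outcome acting on the exposure is not removed by the confounder-adjusted logistic regression described for Primary Aim 1. The appendix's limitations section names misclassification, selection, self-report bias and confounding, but not this. At stake is whether the sub-study reads partner involvement as neutral or harmful when it is neutral or helpful.

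**Working it through.** **1. The plan's own power figure.** Two-sided 5% test of two proportions:

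power = Φ{[|p1 − p2| − 1.96·√(p̄(1−p̄)(1/n1+1/n2))] / √(p1(1−p1)/n1 + p2(1−p2)/n2)}

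Take p1 = 0.12, p2 = 0.06, N = 2,237 and 20% highly involved (n = 1,789.6 and 447.4, p̄ = 0.108). The null SE is 0.01641 and the alternative SE 0.01360, so power = Φ[(0.06 − 0.03216)/0.01360] = Φ(2.05) = 98%. The three splits give about 98%, 99.8% and 99.9%. With one arm only (N = 1,118) they give 78–83%, 93% and 94%. No single N gives 90% throughout; at N = 2,237 the stated 90% is met as a lower bound. The point does not turn on this figure.

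**2. Timing.** 2,237 − 1,160 = 1,077 women, and 1,077/2,237 = 48%, have no Month 3 form. With average follow-up of 18 months, 12/18 = two thirds of follow-up precedes the Month 12 form.

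**3. Partner attendance as the exposure, no true effect.** From the protocol: N = 2,237, infection 12%, about 1–3% of partners attending. Assumed: a share q (1% or 2%) attends for other reasons, and a share s of infected women's partners attends because of the infection.

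- Attenders = Nq + N(1−q)(0.12)s
- Infected among attenders = 0.12Nq + N(1−q)(0.12)s

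For q = 1%, s = 1%: attenders 22.4 + 2.7 = 25.0; infected 2.7 + 2.7 = 5.3, or 21.3%. Among the rest, 11.9% are infected. Apparent risk ratio (RR) 1.8.

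For q = 2%, s = 5%: attenders 44.7 + 13.2 = 57.9; infected 5.4 + 13.2 = 18.5, or 32.0%, against 11.5%. RR 2.8.

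| s | apparent RR (q = 2% to 1%) | simulated rejection (nominal 5%) |
|---|---|---|
| 1% | 1.4–1.8 | 22–33% |
| 2% | 1.8–2.4 | 51–69% |
| 5% | 2.8–3.9 | 98–99.6% |

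Total attendance in these cases is about 1.1–2.6%, inside the protocol's 1–3%. With a true halving of risk and s = 5%, the apparent RR is 2.4–3.6, and significant harm appears in 89–99% of simulated studies.

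**4. Month 12 form as the exposure for everyone.** Assumed: a share s of low-involvement women infected before the form (12% × 2/3 = 8%) is recorded as high. Women moved = N(1−h)(0.08)s, where h is the true share highly involved.

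For h = 20%, s = 20%: 1,789.6 × 0.08 × 0.2 = 28.6 women move. With no effect, high = (53.7 + 28.6)/476.0 = 17.3% and low = (214.8 − 28.6)/1,761.0 = 10.6%; RR 1.64. With a true halving, high = (26.8 + 28.6)/476.0 = 11.7%; RR 1.10.

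| h | s | no effect: RR | rejection | true halving: RR |
|---|---|---|---|---|
| 20% | 10% | 1.30 | 53% | 0.79 |
| 20% | 20% | 1.64 | 97% | 1.10 |
| 50% | 10% | 1.12 | 18% | 0.60 |
| 50% | 20% | 1.27 | 54% | 0.71 |
| 80% | 10% | 1.08 | 8% | 0.55 |
| 80% | 20% | 1.17 | 17% | 0.60 |

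**5. A less extreme form scenario.** Section 10.2 allows 14 days for STI PCR results, so an STI found in the sample taken at the form visit cannot influence the answers. Using Month 3 forms where they exist, and allowing for that delay, simulated rejection is about 6–43% for shifts of 10–20%. The upper end moves with how same-day HIV results are treated.

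**6. After the fix.** Starting at the form, dropping women already infected and counting later infections only gives about 4.5–6% rejection at shifts of 0–20%.

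**The case against.** The strongest reply is that nothing is yet fixed enough to be wrong. The aim is worded as something that could be done and may only suggest relationships. The involvement measures are said not to be pre-constructed. The clinic-visit variable is proposed by name for adherence, and at 1–3% attendance it cannot be the high/low contrast that the power statement describes. The form has 58 questions, and only the testing-invitation item is quoted as one an infection could plainly change. Invitations are offered to all women, so one need not follow an infection. Every response and shift rate above is assumed.

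Much of this stands as a limit on size. It does not remove the defect. The appendix says its data analysis section describes how each aim will be addressed, so time order is not a detail deferred elsewhere. One sentence there carries the involvement variables, including services used, over to biological outcomes. The hedging in Aim 3 concerns low power, not bias.

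A reader might infer more: that the test is bound to reject under no effect and will turn a real benefit into apparent harm. The documents do not support that. They give no response rates. With a form-based measure and a true halving, the ratio crosses 1 between a 10% and a 20% shift when 20% of women are highly involved, only near a 50% shift at 50%, and not even then at 80% (RR 0.83). Disclosure of HIV could also reduce a partner's support, so the direction for form answers is not certain.

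**Conclusion.** The concern holds in limited form. As written, Aim 3 lets the outcome influence the exposure, so its test is not at the nominal level under no effect, and a protective association is biased toward or past the null. The mechanism is in the text; its size is not. On the assumptions shown, inflation is modest to substantial for a form-based measure (about 6–43%) and severe for an attendance variable even if only 1–5% of infected women's partners respond. Sign reversal is plausible mainly for attendance, or when few women are highly involved and about a fifth or more of infected low-involvement women change category. The aim is secondary, in an ancillary observational study, and no primary trial result depends on it.

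**What to change.** For Aim 3, state that:

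- involvement is defined only from information recorded up to the woman's first available form (Month 3 where there is one, otherwise Month 12), including partner visits before that form;
- women with an incident infection already detected by then, or found in the sample taken at that visit, are excluded;
- only infections first detected afterwards count, with person-time starting at the form;
- partner attendance, if analysed itself, is time-varying: a visit counts only for infections detected after it;
- the detectable effect is restated for the smaller number of infections.

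Simply deleting partner visits after the woman's first positive result is not a substitute. It gives infected women less time in which to count as involved. With no effect and no notification, it produced an apparent RR of about 0.5 and 18–35% rejection at 2–3% attendance. Separating visits by reason would also need data the protocol does not say are recorded.

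The change costs analysis work and infections. Ignoring exclusions, woman-years at risk fall from 2,237 × 1.5 = 3,355.5 to 1,160 × 1.25 + 1,077 × 0.5 = 1,988.5, or 59%. Reading 12% as annual, simulated power for a halving is about 70–92% if all women start at Month 12, and roughly 92–99% if Month 3 forms are used where available. It is lower if 12% is meant over the whole follow-up. The time-varying analysis needs partner visit dates. Secondary Aim 4 already plans to identify visits falling between forms, but the availability of dates should be confirmed.
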